### Data collection methods

Baseline characteristics collected from electronic patient files include age, gender, clinical and histological tumour data, (surgical) history and comorbidities. Comorbidities are graded using the Adult Comorbidity Evaluation (ACE-27) as none, mild, moderate or severe [29]. Follow-up data will be collected via patient files or surveys and stored in REDCap (Table 1). Only the researchers have access to this securely stored data.

Patients will complete a 39-question survey at baseline (Supplementary information C) and again at 6 and 12 months. The survey includes validated and new questions, developed with support from a clinical epidemiologist (KV) with expertise in questionnaires (Table 1) [30–35].

The baseline survey is completed on paper after inclusion but before randomisation. A shorter version is used during follow-up. Intervention group patients receive surveys at baseline or by mail and complete them during a scheduled call with researcher assistance if required. Patients followed at the HNOC complete surveys after follow-up visits, also with help if required.

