### Outcomes

Our primary outcome is satisfaction with care and is measured on a 0–10 numeric rating scale (NRS) at 12 months post-inclusion. Our secondary outcome is safety, which is evaluated and measured by recurrence, re-referral rate, complications following recurrence treatment and survival. For the secondary outcomes, patients will be followed for at least 1 year after inclusion. Safety outcomes are only assessed after the study termination, thereby aiming for at least 2 years follow-up per patient. All outcome measures are outlined in Table 1.

**Table 1 T0001:** Outcome measures.

Outcome measure	Assessment	Evaluation method	Timing of evaluation

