**Patient satisfaction (PREMs)**			
Overall satisfaction with care	0–10 NRS	Survey	Baseline, at 6 and 12 months
**Satisfaction with travel time**	0–10 NRS	Survey	Baseline, at 6 and 12 months
**Specific satisfaction**	Questions about satisfaction with care from CQI questionnaires [33, 35]	Survey	Baseline, at 6 and 12 months

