## Discussion and conclusion

This is the first prospective study investigating the novel concept of relocating follow-up care for HNC patients. Since the COVID-19 pandemic, telemedicine use has notably increased and is widely accepted by both oncologic and non-oncologic patients [26–28, 38]. In most telemedicine studies in otolaryngology, videoconferencing consultations are used, with remote physical examinations occasionally employed for otoscopic evaluations but not for laryngoscopic (follow-up) assessments [39, 40]. Advancements in HD-laryngoscopy and emerging Artificial Intelligence (AI) disease detection software may create opportunities to reorganise follow-up care for HNC patients, reducing dependency on physician expertise [41, 42].

The strength of the study is its RCT design and the inclusion of a preference arm. This study aligns with sustainability goals. The possibility of telemedicine follow-up offers a more flexible and patient-centred approach to care, reducing travel burden and increasing accessibility. It may also help alleviate pressure on specialised centres by enabling efficient, remote monitoring without compromising safety. A limitation of the study is the use of a non-validated survey. However, most questions are derived from validated questionnaires, and the benefit of validation of the survey was not seen. Additionally, patients in the intervention group will complete the survey in a different setting than those in the control group (i.e. at home with remote assistance through a telephone call and at the HNOC with assistance in person as needed), which may introduce bias. With the knowledge that a follow-up duration of 12 months is limited, safety outcomes will only be assessed after the conclusion of the study period. Furthermore, travel distances to hospitals in the Netherlands are typically shorter than in other countries; however, the findings of this study may also be applicable to larger countries, where they could potentially benefit an even greater number of patients. If patients are satisfied and safety is confirmed, future research should explore other patient groups suitable for telemedicine follow-up. Multicentre studies will be necessary to assess its national impact and inform guideline changes, benefiting patients, society and the environment.

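### Follow-up satisfaction surveys are completed at home with telephone help in one arm and at the HNOC with in-person help in the other, so survey mode is confounded with allocation

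*Protocol article*

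**What the plan says.** All places are in the protocol article.

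- **Outcomes:** "Our primary outcome is satisfaction with care and is measured on a 0–10 numeric rating scale (NRS) at 12 months post-inclusion". Table 1 lists overall satisfaction as a survey item with timing "Baseline, at 6 and 12 months".
- **Data collection methods, baseline:** "The baseline survey is completed on paper after inclusion but before randomisation".
- **Data collection methods, intervention arm:** "Intervention group patients receive surveys at baseline or by mail and complete them during a scheduled call with researcher assistance if required".
- **Data collection methods, patients followed at the HNOC:** "Patients followed at the HNOC complete surveys after follow-up visits, also with help if required".
- **Discussion and conclusion:** the authors state that "patients in the intervention group will complete the survey in a different setting than those in the control group" and describe the two settings as "at home with remote assistance through a telephone call and at the HNOC with assistance in person as needed), which may introduce bias".
- **Allocation to study groups:** 1:1, with no blinding after randomisation.
- **Statistical analysis:** an independent t-test or Mann-Whitney test between groups, intention-to-treat, with multiple imputation for missing values. Nothing there concerns how the survey was completed.

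**The concern.** A self-rated satisfaction score can depend on where it is given and who is at hand to help. Here both differ by arm after randomisation, and the score is the sole primary outcome. The setting also bears on the construct itself: controls rate their care inside the institution that provides it, and intervention patients rate theirs at home.

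The shift could go either way. Reluctance to criticise while on site could raise control scores, and a recent long journey could lower them. Both mechanisms are conjecture, since the article gives no evidence for either.

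At stake is the meaning of the primary comparison. A positive result could be partly a mode effect, and a null result could hide a benefit. Lack of blinding is inherent in this trial. The difference in survey procedure is not, because a mail-and-call route already exists in one arm.

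**Working it through.** **1. The two procedures side by side**

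| Feature | Intervention | Control | Source |
|---|---|---|---|
| Baseline survey | paper, before randomisation | same | Data collection methods |
| Place at 6 and 12 months | home | HNOC | Discussion and conclusion |
| Help | by telephone, if required | in person, if required | Data collection methods; Discussion and conclusion |
| Timing relative to a visit | not stated | after a visit, interval not stated | Data collection methods |

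Place and type of help differ by arm. Timing may differ, but the text does not settle it.

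**2. Can anything in the plan separate mode from treatment?**

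- *Adjustment for mode:* no. Under the stated procedure every intervention survey has one mode and every control survey the other, so a mode term cannot be estimated alongside the arm term.
- *Baseline score:* no. It is collected the same way in everyone, before the modes diverge.
- *Preference group:* no. It is followed at the HNOC, so it falls under the control procedure, and it is not randomised.
- *Intention-to-treat, imputation or more patients:* no. The expected estimate is the treatment effect plus the mode shift b at any sample size.

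An analysis plan that is not shown could not repair this either, because the data would hold no information on b.

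**3. The plan's own figure**

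Inputs from Sample size and recruitment: difference 1, SD 1.8, power 80%, two-sided alpha 0.05, stated n = 41 per group.

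- Two-sided: n = 2(1.960 + 0.842)² × 1.8² / 1² ≈ 50.9, so 51 per group (52 with the t distribution).
- One-sided: n = 2(1.645 + 0.842)² × 1.8² / 1² ≈ 40.1, so 41 per group.

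The stated 41 matches a one-sided test. At 41 per group the two-sided t-test has about 70% power. That is a separate matter and does not affect the confounding. I use 41 below because it is the number the plan expects to analyse.

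**4. What an assumed mode shift would do**

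The documents give no value for b, so the shifts below are assumptions.

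- SE of the difference = 1.8 × √(2/41) = 0.398.
- Noncentrality = (true difference + b) / 0.398, with 80 degrees of freedom.
- The rejection probability is the two-tailed area of the noncentral t beyond the 5% critical values.

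| Assumed size of b (points) | b / SE | False-positive rate, no true difference | Power for a true 1-point effect, b against the intervention | Same, b in favour |
|---|---|---|---|---|
| 0 | 0 | 5.0% | 70.0% | 70.0% |
| 0.1 | 0.25 | 5.7% | 60.9% | 78.0% |
| 0.3 | 0.75 | 11.6% | 41.3% | 89.8% |
| 0.5 | 1.26 | 23.7% | 23.7% | 96.1% |

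With 45 per arm the false-positive rates are 5.8%, 12.2% and 25.6% for the same three shifts. More patients make the distortion slightly worse.

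**The case against.** **The authors already disclose it.** This is true, and the article does not contradict itself here. But it offers no remedy, and disclosure does not remove a bias that could be avoided.

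**The timing difference is not documented.** A reader might infer that controls rate their care immediately after a visit while the intervention call is unrelated to any visit. The text supports neither. It gives no interval for controls and does not say how the call relates to a visit. Under Interventions, the HNOC also contacts intervention patients after the same-day video assessment, so some contact around visits exists. An article may leave survey windows to the full protocol. Timing is therefore only a possible further difference.

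**The difference in help may be modest.** Help is optional in both arms, and intervention patients have the questionnaire in hand. Reading this as interviewer-administered versus self-administered goes too far. For patients who need no help, the documented difference is mainly place and the presence of a call. The article also does not say who assists controls, so a courtesy effect towards treating staff is an assumption.

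**The size is assumed.** This stands. At 0.1 points the false-positive rate is close to nominal.

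**Some subjectivity is unavoidable.** Patients know their arm and are rating the care model itself. A common procedure removes one added source of bias, not all of it.

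What remains is that place and type of help are fixed by arm for the primary outcome, and the data cannot show what that contributes.

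**Conclusion.** The point holds for place and type of assistance. Both are fully confounded with allocation at 6 and 12 months, and so for the primary outcome, and no planned analysis can separate them.

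The size and direction of any mode effect are unknown. With SD 1.8, 41 per arm, a two-sided t-test and no true difference, assumed shifts of 0.1, 0.3 and 0.5 points give false-positive rates of about 6%, 12% and 24%. These figures show sensitivity and do not estimate the bias.

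A reader might conclude that the primary result will be invalid or will favour telemedicine. The article supports neither: it establishes a risk of bias, and a shift could equally hide a benefit. Because the risk is disclosed and of unknown size, but avoidable at low cost, this is a should-fix.

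**What to change.** For all remaining 6- and 12-month surveys, use one procedure in both arms:

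- mail the survey to the home;
- have it completed at home in the same window relative to a follow-up visit;
- offer the same optional researcher call;
- record the mode of each survey.

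For control surveys already completed on site, report mode by arm and state that the mode effect cannot be separated for them. Restricting the analysis to same-mode surveys does not rescue these data, since no control survey completed on site shares the intervention mode. A comparison limited to surveys collected after the switch would use only controls surveyed later and should be labelled exploratory. The switch also leaves mixed modes within the control arm, which the report should say.

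**Cost:** an amendment to data collection, and at most two mailings to each of about 45 controls (90 / 2), or about 90 mailings, plus calls for those who want one. Control response may be slightly lower than with on-site completion and should be watched against the 10% drop-out allowance. The sample size does not change on this account.

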### Statistical analysis

Descriptive statistics will be used to summarise patient’s baseline characteristics. Categorical variables will be presented as absolute numbers and percentages of the total. Continuous variables are tested for normality using Kolmogorov-Smirnov analysis and will be presented as means and SDs for normally distributed data, and medians and interquartile ranges for non-normally distributed data. Between-group mean (or median) differences, rate differences and rate ratios with 95% confidence intervals (or ranges) will be calculated. The groups will be compared using the Wilcoxon signed rank test or the Mann-Whitney test for non-normally distributed data, the independent t-test for normally distributed data and chi-squared test for categorical variables. Additionally, within-group changes will be assessed with paired t-tests (continuous data) and the McNemar test (categorical data). Kaplan-Meier survival analysis will be performed for disease-specific and overall survival. The EQ-5D-5L, EORTC QLQ-H&N-35 and cancer worry scale (CWS) questionnaires will be analysed according to their manual [30–32, 34]. Total CO_2_ emission caused by travel to the hospital will be estimated and compared between groups based on the values provided by the European Environment Agency for the period 2010–2023 (130.1 g of CO_2_ per kilometre) [36]. Missing values will be handled using multiple imputation, assuming that there is only missingness at random, and all analyses will be performed on an intention-to-treat basis. The data will be reported according to the CONSORT guidelines [37].

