### Sample size and recruitment

A power analysis was performed to calculate the sample size needed to answer our primary research question. As telemedicine follow-up has not been studied in HNC patients, power analysis was based on data from non-oncologic populations [26–28]. Most of these studies are one-armed studies. These studies reported a mean patient satisfaction, measured with a NRS or VAS, of 8.6 to 8.8, with one study noting a baseline score of 8.2. Although these results may not be representative of the HNC population, we based our expectations with regard to the primary outcome on these studies, nonetheless. Patient satisfaction is estimated at 9 (standard deviation [SD] 1.8) in the intervention arm and 8 (SD 1.8) in the control arm. To detect a clinically relevant difference of 1 point with 80% power and a two-sided alpha of 0.05, at least 41 patients per group are required. With an expected drop-out of 10%, a total of 90 patients will be included. This analysis was performed using G*Power (version 3, Heinrich-Heine-Universität Düsseldorf, Germany). Patients are first informed about the study by their treating head and neck oncologist in the HNOC. If a patient meets the eligibility criteria, the researcher will provide additional information, and an informed consent will be obtained.

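### The primary effect is planned as a 1-point mean difference, but a normality test can switch it to a median difference reported with a range

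*Protocol article*

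**What the plan says.** The Outcomes section makes satisfaction with care the primary outcome, "measured on a 0–10 numeric rating scale (NRS) at 12 months post-inclusion". The Sample size and recruitment section sets its planning values: "Patient satisfaction is estimated at 9 (standard deviation [SD] 1.8) in the intervention arm and 8 (SD 1.8) in the control arm". The target is stated on the same scale: "To detect a clinically relevant difference of 1 point with 80% power and a two-sided alpha of 0.05". So both the clinical criterion and the sample size concern a difference in means.

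The Statistical analysis section then gives one rule for all continuous outcomes: "Continuous variables are tested for normality using Kolmogorov-Smirnov analysis". If normality is accepted, means, SDs and the independent t-test follow. If it is rejected, medians, interquartile ranges and a rank test follow. The effect measure is set in the same general way: "Between-group mean (or median) differences, rate differences and rate ratios with 95% confidence intervals (or ranges) will be calculated". Nothing in the article says that the primary outcome is handled differently, or that a mean difference with a confidence interval is reported whatever the normality test shows.

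**The concern.** If the rule sends the primary outcome down the non-normal branch, the reported effect is no longer on the scale on which 1 point was declared relevant. A difference in medians on an 11-point integer scale moves in coarse steps and need not resemble the difference in means. The Mann-Whitney test does not in general test a difference in medians either, so the p-value and the reported effect would answer different questions.

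The bracketed alternative of ranges adds to this. It parallels the bracketed alternative of medians, so it can be read as giving ranges to median differences. A range describes the spread of observations. It does not say how precisely a difference between arms is known. A reader could then not judge whether the trial's result is compatible with 1 point.

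**Working it through.** **Inputs.** From the article: scale 0–10; means 9 and 8; SD 1.8 in both arms; 41 per arm; two-sided alpha 0.05; 80% power. Assumed: whole-number scores, and the shapes of the distributions in step 4.

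**1. The plan's own figure.** The normal approximation for two means is n = 2(z₁ + z₂)²·SD²/difference².
- Two-sided: 2 × (1.960 + 0.842)² × 3.24 / 1 = 50.9, so 51 per arm (52 with the exact t calculation).
- One-sided: 2 × (1.645 + 0.842)² × 3.24 / 1 = 40.1, so 41 per arm (40.8 with the exact t calculation).

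The stated 41 thus reproduces only as a one-sided figure. Two-sided t-test power is 70.0% at 41 and 74.1% at 45 per arm. This is a separate matter, but it bears on the cost of the fix.

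**2. Does the intervention arm pass the normality test?** At the ceiling of 10 the empirical distribution function equals 1. The fitted normal there equals Φ((10 − 9)/1.8) = Φ(0.556) = 0.711. So D ≥ 1 − 0.711 = 0.289 for any data with that mean, SD and cap, whatever their shape. The 5% critical value at n = 41 is about 1.36/√41 = 0.212 for the plain KS test and about 0.138 for the Lilliefors version. Normality is rejected by either.

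The article does not say whether the test is run by arm or pooled. Pooled, the mean is 8.5 and the SD is √(3.24 + 0.25) = 1.868, so D ≥ 1 − Φ(1.5/1.868) = 0.211, against about 1.36/√82 = 0.150. That fails too. In the control arm alone the bound is 1 − Φ(2/1.8) = 0.133, which forces nothing.

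**3. How many patients must score 10?** Let Y = 10 − score, so E[Y] = 1 and E[Y²] = 3.24 + 1 = 4.24.
- (Y − 1)(Y − 10) is 10 at Y = 0 and at most 0 at the other whole numbers. Its mean is 4.24 − 11 + 10 = 3.24, so the share at 10 is at least 0.324.
- (Y − 4)(Y − 5) is 20 at Y = 0 and at least 0 at the other whole numbers. Its mean is 4.24 − 9 + 20 = 15.24, so the share at 10 is at most 0.762.

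The planning values thus allow 32% to 76% at the ceiling. The shape within that span is not known.

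**4. What would the median difference show?** Trials with 41 per arm were simulated from integer distributions matching both planned means and SDs, so the true mean difference is 1.0. Across assumed shapes the sample median difference was 0 in about 1–49% of trials, 1 in 33–48% and 2 in 5–64%. Separate simulations of individual shapes show what drives this, and move the ends by a few points:

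| Share at 10 (intervention / control) | Difference 0 | 1 | 2 |
|---|---|---|---|
| 66% / 28% | about 1% | 27% | 69% |
| 63% / 23% | about 2% | 38% | 60% |
| 50% / 20% | 21% | 51% | 28% |
| 40% / 15% | 51% | most of the rest | 5% |

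**5. What would the mean difference show?** The expected 95% half-width is t × 1.8 × √(2/n). At 41 per arm it is 1.990 × 0.398 = 0.79 points; at 45 per arm it is 1.987 × 0.379 = 0.75. Either can be read directly against 1 point.

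**The case against.** The strongest reply is that the article is a condensed text with a general rule, that the rule is conditional, and that the non-normal branch may serve the hypothesis test well. Much of this stands.

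- **Power.** Under the two shapes with 63–66% at 10, the t-test has about 70% power and Mann-Whitney about 90% or more. Moving to the rank test is then a gain. The harm lies in how the effect is reported.
- **A test picked from the data.** A reader might infer that the gate leaves the choice of test to chance. Under the planning values it does not: rejection is practically certain, so the test is in effect fixed. The choice becomes uncertain only if the planning values fail. With normal scores clipped at 10 and recorded in 0.1 steps (means near 8.7 and 7.9, smaller SDs), normality was rejected in at least one arm in 93% of trials by Lilliefors but in 19–22% by plain KS.
- **Share at the ceiling.** A reader might infer that mean 9 and SD 1.8 require about two thirds of patients at 10. Step 3 shows that they do not.
- **Direction.** A reader might infer that the median difference will exaggerate the effect. Whether it tends towards 2 or 0 depends on the shape, so only its instability is established.
- **Ranges.** A reader might infer that the primary result will carry no confidence interval. The sentence covers all outcomes and does not say so. It permits a range, and that permission is the fault.
- **Multiple imputation.** A reader might add that rank tests and medians pool awkwardly over imputed data sets. The article fixes no wrong pooling rule, and this can be left to an analysis plan.

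Brevity does not answer the core point. The article states a rule for the effect measure and its interval, and that rule conflicts with its own definition of the target.

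**Conclusion.** The point holds. The article sets its criterion as a 1-point mean difference and then states a rule that, at its own planning values, reports a median difference and permits a range in place of a confidence interval. Failure of the normality test in the intervention arm needs no assumption about shape, only a sample mean and SD near 9 and 1.8 and the cap of 10 (D at least 0.289 against about 0.21). The spread of the median difference (0 in about 1–49% of trials, 1 in 33–48%, 2 in 5–64%) rests on assumed integer distributions and shows instability, not bias in a known direction. The documents do not show that the test decision would be invalid or that power would be lost under the present rule.

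**What to change.** For the primary outcome:
- Drop the normality gate. Report the between-group mean difference at 12 months with a 95% confidence interval whatever the distribution, using a robust or bootstrap standard error and preferably adjusting for the baseline score, which is already collected.
- Delete ranges as an alternative to confidence intervals for any between-group difference.
- Name a single hypothesis test in advance. If it is not Mann-Whitney, report Mann-Whitney with a Hodges-Lehmann confidence interval alongside.

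The cost is a few sentences in the Statistical analysis section and no new data. The choice of test is a real trade-off: a mean-based primary test matches the 1-point criterion, but its unadjusted power at 41 per arm is about 70%, below the stated 80%, and under ceiling effects it can be lower than that of the rank test. Baseline adjustment may recover some of this; the amount was not computed. Reporting the mean difference with its interval is worthwhile whichever test is named.

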### Interventions

Figure 1 visualises the study flow. Included patients will be randomly assigned to one of two groups: an intervention group and a control group. Follow-up is performed though standardised follow-up guidelines and is equal for all patients, with at least of 4 to 6 consultations expected [4]. The control group will receive their oncological follow-up in the UMCG. The intervention group will receive their oncological follow-up by an ENT surgeon in a hospital that is closer to the patients’ home. A reduction in travel time of more than one-third was considered indicative of closer proximity to home, as it is believed that it would be a significant time reduction for the patients. A history will be taken, and a complete ENT physical examination will be performed, including flexible HD-video laryngopharyngoscopy (with or without NBI) and neck palpation. HD-laryngopharyngoscopy is performed with digital transnasal flexible endoscopes of XION (XION GmbH, Berlin, Germany) or Olympus (Olympus Nederland BV). The videos obtained during the follow-up visit will be digitally transferred and securely stored in the electronic patient files in the HNOC, for the same day assessment by a head and neck oncologist. Furthermore, the head and neck oncologist has access to the patients’ previous examinations, (surgical) history and findings or concerns of the ENT surgeon who has seen the patient earlier that day. After evaluation, the patient is contacted by the HNOC to share the results, and a new management plan (such as re-referral to the HNOC) is formulated if necessary.

Patients who do not wish to participate in this randomised controlled study will be asked to complete the questionnaires that are part of this study whilst receiving their follow-up in HNOC (the ‘preference group’).

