**PROMs**			
HRQoL	EQ-5D-5L questionnaire, assesses five dimensions of health: mobility (1), self-care (2), usual activities (3), pain/discomfort (4), and anxiety/depression (5) [31, 32]. Each dimension is rated on a 5-level scale, ranging from no problems (1) to extreme problems (5). Additionally, the EQ-5D-5L includes include a 0–100 VAS.	Survey	Baseline, at 6 and 12 months
**Symptom burden**	Four subdomains of the EORTC QLQ-H&N-35 questionnaire (weight loss, speech, swallowing function and pain) [30]. The H&N35 employs a 4-point response scale (‘not at all’ to ‘very much’), with higher scores indicating a higher symptom burden.	Survey	Baseline, at 6 and 12 months
**Fear of recurrence**	CWS, 6 items on worries after cancer treatment rated on a 4-point scale from almost never/ not at all to almost always/ very much [34].	Survey	Baseline, at 6 and 12 months

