### Allocation to study groups

An independent researcher will generate the randomisation chart to ensure allocation concealment for the patient, clinician and researcher. Randomisation will be performed in REDCap with a 1:1 allocation ratio. Block randomisation and stratification will not be used, as no baseline characteristics are expected to significantly influence the study outcomes. Blinding of the treatment allocation after randomisation is not feasible, as both patients and care providers will be aware of the hospital setting in which the follow-up takes place.

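### The Wilcoxon signed-rank test, a paired test, is listed for comparing the two independent randomised groups

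*Protocol article*

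**What the plan says.** The design has two separate groups: "Included patients will be randomly assigned to one of two groups: an intervention group and a control group" (Interventions). On allocation the article states "Randomisation will be performed in REDCap with a 1:1 allocation ratio" and rules out both blocking and stratification (Allocation to study groups). No matching of patients is described anywhere.

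Under Statistical analysis the choice of test depends on distribution: "Continuous variables are tested for normality using Kolmogorov-Smirnov analysis". For the non-normal branch, "The groups will be compared using the Wilcoxon signed rank test or the Mann-Whitney test for non-normally distributed data". The sentence goes on to name "the independent t-test for normally distributed data and chi-squared test for categorical variables". A separate sentence covers change over time: "within-group changes will be assessed with paired t-tests (continuous data) and the McNemar test (categorical data". For the EQ-5D-5L, QLQ-H&N-35 and cancer worry scale, the article says the "questionnaires will be analysed according to their manual".

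The primary outcome is overall satisfaction on a 0-10 scale at 12 months (Outcomes). The sample-size section plans for means of 9 and 8 with SD 1.8 in each arm and 41 patients per group.

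**The concern.** The signed-rank test ranks within-pair differences. Between two independently randomised arms there are no pairs, so the test has no defined input. The sentence joins it to Mann-Whitney with a plain *or* and gives no rule for choosing. A reader cannot take it as meant for change over time, because within-group tests have their own sentence directly afterwards.

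This matters because the primary outcome will probably be analysed in this branch. As written, the plan for the main comparison of an open-label trial contains one test that does not fit the design, and an unresolved choice between two tests. If signed-rank were used, its result would depend on how patients happened to be ordered in the data file, and some power could be lost.

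**Working it through.** **1. Does the design supply pairs?** Interventions describes two randomised groups, and Allocation to study groups describes 1:1 allocation without blocks or strata. Neither section mentions matching. A paired between-group test therefore has nothing to pair on.

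**2. Is the non-normal branch likely for the primary outcome?** Inputs from the sample-size section: mean 9, SD 1.8; scale maximum 10. One SD above the mean is 9 + 1.8 = 10.8, beyond the end of the scale. A normal distribution would put the share above (10 − 9)/1.8 = 0.56 SD, about 29%, at impossible values. A score with these moments must be left-skewed. In a simulation of 41 patients per arm with two bounded shapes that keep the planned moments, the Kolmogorov-Smirnov test rejected normality in the intervention arm in all 3,000 runs.

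**3. How often would the arms even be equal?** With N = 90 and each patient allocated independently with probability 1/2:

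P(45:45) = C(90,45) / 2^90 = 0.0839, or 8.4%.

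In the other 91.6% of cases the arms differ in size, and a one-to-one pairing cannot use every patient.

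**4. What if patients were paired arbitrarily?** Simulation with 41 per arm, two-sided 0.05. The score shapes are assumptions, since the article gives only means and SDs. The ranges are over repeated runs.

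| Assumed 0-10 score shape | Mann-Whitney power | Arbitrary-pair signed-rank power | Loss (points) |
|---|---|---|---|
| Beta-binomial, means 9 and 8, SD 1.8 | 92-93% | 75-77% | 15-18 |
| Rounded normal refitted to means 9 and 8, SD 1.8 | 90% | 72-74% | 16-18 |
| Normal (9 and 8, SD 1.8) rounded and clipped, not refitted | 64-65% | 62-64% | 1-2 |

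The third shape does not keep the planned figures: after clipping, the means are 8.68 and 7.88 and the SDs 1.40 and 1.63. It is shown because it marks the low end of the range.

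With no true difference, the arbitrary-pair signed-rank test rejected in 4.5% to 5.1% of runs, so type I error is not inflated.

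**5. How far does the p-value depend on the pairing?** Three simulated data sets, each held fixed while the pairing was reshuffled:

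| Mann-Whitney p | Signed-rank p, lowest to highest over pairings |
|---|---|
| 0.00018 | 0.000017 to 0.0038 (2,000 pairings) |
| 0.007 | 0.003 to 0.075 |
| 0.019 | 0.075 to 0.58 (1,000 pairings) |

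In the second data set the conclusion at 0.05 changes with the ordering. In the third, the signed-rank test never agrees with Mann-Whitney.

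**The case against.** The best defence is that no reading leaves the trial without a valid test. Mann-Whitney is named in the same sentence, and the independent t-test covers the normal branch. With unequal arms, signed-rank could not be run on all patients, so in practice the choice mostly resolves itself. The wording may be a slip for the rank-sum test, which is Mann-Whitney under another name, or a within-group test placed one sentence too early. The article proposes no pairing, and the power loss is small under one plausible shape. All of this stands and keeps the point modest. It does not remove it: the sentence as printed is wrong, and nothing else in the article corrects it.

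A reader might also infer that the within-group sentence is wrong, with the paired t-test applied to skewed scores and McNemar to multi-level items. The article does not say so. It names these tests for continuous and categorical data without further branches. The paired t-test needs roughly normal differences, not normal raw scores, and is fairly robust at about 41 to 45 pairs. McNemar is correct for binary items. The EQ-5D-5L dimensions ("Each dimension is rated on a 5-level scale, ranging from no problems (1) to extreme problems (5") and the 4-point scales belong to instruments that are to be analysed by their manuals. The general rules do cover the satisfaction ratings and the CQI questions, but the article does not show the CQI response format. These are at most incomplete branches, which a condensed article may leave to a fuller plan.

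**Conclusion.** The point holds for one test: signed-rank is misassigned to an unpaired between-group comparison, in the branch the primary outcome is likely to enter. It should be corrected, but it does not threaten the trial.

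The 8.4% figure rests on reading the absence of blocks as simple randomisation. If the allocation list happened to be fixed at 45 and 45, the arms would be equal but there would still be no pairs, so the conclusion does not depend on it. The loss of power, from 1 to 2 points up to 15 to 18 points, depends on the assumed score shape and should be quoted only as a range. It is at the upper end for the two shapes that keep the planned means and SD.

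Two stronger conclusions are not supported. The primary comparison is not left without a valid test, because Mann-Whitney is named. The false-positive rate is not raised by arbitrary pairing.

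**What to change.** In the between-group sentence, delete the signed-rank test, so that Mann-Whitney is the only rank test for comparing the arms. In the within-group sentence, add the signed-rank test for change scores that are not approximately normal. Possible wording: *The two groups will be compared with the Mann-Whitney test for non-normal data, the independent t-test for normal data and the chi-squared test for categorical data. Within-group change will be assessed with the paired t-test, or the Wilcoxon signed-rank test where change scores are non-normal, and with the McNemar test for binary items.* Limiting McNemar to binary items here is a clarification, not the correction of an error.

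The cost is two sentences. Sample size, data collection and conduct do not change. The edit should be made before outcome data are compared by group, so that the test is fixed in advance.
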